**Health insurance perspective**			
Utilization: Hospital stays and emergency responses	Number of hospital stays/ emergency responses	Claims data	primary
Utilization: Ambulatory-care sensitive hospital stays and emergency responses	Ambulatory-care sensitive diagnoses	Claims data	primary
Utilization: ambulatory resource allocation	Ambulatory medical utilization	Claims data	secondary
Cost: New form of healthcare	All costs directed towards the new form of healthcare	Diary and claims data	primary
Cost: Comparison of new form of healthcare versus standard care	Comparison with saved costs of standard care	Diary and claims data	primary
**Patient perspective**			
Health	QoL-AD; own design of questions	Diary data and SoSci Survey	secondary
Well-being	WHO-5; OSSS-3; UCLA-LS	Diary data and SoSci Survey	secondary
Care dependency	Barthel-Index	Diary data and SoSci Survey	secondary
**Healthcare provider perspective**			
Interdisciplinary cooperation	Own design of questions	Diary data	secondary
Suitability of tasks	Own design of questions	Diary data	secondary
Usability	BGW	Diary data	secondary

#### Health insurance perspective

On the level of the health insurance, utilization and total costs will be compared between intervention group and control group 1. Concerning utilization, number of hospital stays, days spent in inpatient hospital care, and number of emergency situations will be analyzed. For these measures, a second analysis will focus on ambulatory-care sensitive hospital stays and emergency responses [13, 19]. Furthermore, the volume of healthcare provided by the outpatient sector will be evaluated. For the economic evaluation, the total costs of the new form of healthcare in addition to costs for standard care within the intervention group will be assessed and compared to the costs of standard care for the control group 1 [20–22].

The rationale for selecting the number of treatments (e.g. hospital stays) and the overall treatment costs as the primary outcome domains is based on their direct relevance to the study’s objectives and clinical impact. The number of treatments provides a quantifiable measure of intervention utilization, offering insights into the intensity and frequency of care required. Meanwhile, total treatment costs are essential for evaluating the economic implications of the intervention, which is particularly important for healthcare systems focusing on cost-effectiveness and resource allocation. Together, these domains allow for assessing both the practical and financial viability of the intervention, making them highly pertinent to stakeholders and policymakers.

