###  Participants

 Assuming that the hospitalization rate in the patient group before the intervention is approximately 20 percent [2] with a potential of reduction to 15 percent during intervention (a reduction of 25 percent), with a power of 90 percent and a significance level of 0.05, the calculated sample size is 1,210 patients for the intervention group [18]. To address sample attrition due to heightened mortality in the research group as well as other unforeseeable drop-outs, about 25 percent additional patients should be recruited, resulting in a total sample size of *n* = 1,500 participants in the intervention group, with at least the same number of controls to be drawn. GPs will be recruited through outreach by the KV, which in turn will recruit eligible participants for the study. Alternatively, the participants will be recruited by a study physician to relieve the GPs. The informed consent will be obtained from the participants by either their GP or the study physician. The intervention group will be derived from eligible insurees of the participating health insurance companies, who are 60 years or older, reside in Berlin in their own home, receive support from a caregiver, and have been either officially granted “care level” 1 or higher, have applied for it or been assessed by their GP as needing “care level” 1 or higher. In Germany, five “care levels” represent a scale used to classify the level of care needed by individuals requiring long-term care. The respective care level determines the subsidies those individuals receive through their nursing care insurance provider. Participants can withdraw their consent to participate in the study anytime. If participants stop meeting the inclusion criteria listed above at some point, e.g. leave their participating insurance company, they will be excluded from the study.

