###  Study period

The study period is designed to take place within eight quarters (24 months). During the first six quarters (18 months), the intervention group will be gradually recruited for the new form of healthcare, so that individuals who are added at the end of the recruitment period can utilize the new form of healthcare for at least two quarters (6 months). For the control group 1 and the operationalization of control variables, the claims data of the health insurance companies from a pre-observation period of eight quarters before entry into the new form of healthcare will be used. The surveys on the secondary endpoints take place at the beginning of the intervention (weeks 2-4) and after 3 to 6 months during the intervention. The control group 2 is surveyed at a congruent time interval. Figure 2 illustrates the planned data collection period and the cumulatively increasing sample size of the intervention group.

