## Trial status

Start of recruitment was March 25, 2024, and will continue until June 30, 2025. The observation period will end on December 31, 2025. By the time of submission (November 17, 2024), *n*= 36 participants have already been enrolled in the trial. The results will be reported to the funder, as well as shared with the scientific community and the public in a publication.

Authorship eligibility guidelines within the study consortium are established to ensure that all contributors who meet the criteria for authorship are appropriately credited in publications. Principles of intellectual contribution and accountability in the authorship process are prioritized. There are no intended uses of professional writers for the preparation of manuscripts; instead, all publications will be collaboratively developed by the research team members.

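### Primary utilization and cost outcomes are numbers and totals with no time base, while observation runs from 6 to 21 months and some stated exits can occur only in the intervention group

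*Protocol article*

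**What the plan says.** In Table 1 of the protocol article, the primary utilization outcome is operationalized as "Number of hospital stays/ emergency responses". The text under Outcomes, Health insurance perspective, adds inpatient days: "number of hospital stays, days spent in inpatient hospital care, and number of emergency situations will be analyzed". The same measures are then restricted to ambulatory-care sensitive cases. For the overall comparison it says that "utilization and total costs will be compared between intervention group and control group 1". None of these statements gives a period or a per-time unit.

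Entry is staggered. Under Study period, "The study period is designed to take place within eight quarters (24 months"), with recruitment over the first 18 months, so that late entrants "can utilize the new form of healthcare for at least two quarters (6 months"). Trial status gives recruitment from 25 March 2024 to 30 June 2025, and "The observation period will end on December 31, 2025".

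The section Participants says "Participants can withdraw their consent to participate in the study anytime", and that people who no longer meet the inclusion criteria are excluded; leaving the participating insurer is the example given. The criteria also include living in Berlin in one's own home and having a caregiver. Control group 1 is drawn from the insurers' enrollee and billing data. The article gives it a pre-observation period of eight quarters tied to programme entry, but no follow-up window, outcome start date or exit rule. Under Analysis, the regression models are left to be chosen according to the data.

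**The concern.** A number of stays or a total cost has a fixed meaning only over a fixed period. Here the period differs more than threefold between participants, and the only stated rules that end it early are written for enrolled participants. A member of control group 1 has no consent to withdraw, and nothing says that a control who loses a caregiver or moves out of the home would be removed.

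If these exits shorten observation in the intervention group and the outcomes are compared as Table 1 defines them, stays, inpatient days, emergency responses and costs all come out lower for a reason unrelated to the programme. The error favours the programme and falls on the primary comparison. The Limitations section acknowledges that the two groups are reached differently, but treats this as selection bias and does not mention unequal observation time.

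**Working it through.** **Plan's own figures.** Inputs from Participants: 20% versus 15%, power 90%, significance level 0.05 (taken as two-sided), 1:1.
- Unpooled formula: n = (1.960 + 1.282)² × (0.20×0.80 + 0.15×0.85) / 0.05² = 10.507 × 0.2875 / 0.0025 ≈ 1,208 per group. The pooled form gives 1,212. The stated 1,210 is reproduced.
- Recruitment: 1,500 / 1,210 = 1.24, consistent with about 25 percent extra. As a share of those recruited, the allowance is 1 − 1,210/1,500 = 19.3%, for deaths and other drop-outs together.

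**Observation time.** Inputs from Trial status, to 31 December 2025:
- Entry 25 March 2024: 646 days; 646 / 30.4375 = 21.2 months.
- Entry 30 June 2025: 184 days; 184 / 30.4375 = 6.0 months.
- Ratio 646 / 184 = 3.5.

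**Effect of one-sided exits on a raw count, with no programme effect.** Assumptions: constant event rate; controls take over their match's entry date and are otherwise complete; a share f of the intervention group leaves, on average halfway through its time, independently of risk.

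Mean observed time is T × (1 − f/2) in the intervention group and T in controls, so the ratio of mean counts is 1 − f/2, whatever T and the event rate. If a share g of controls leaves in the same way, it is (1 − f/2) / (1 − g/2).

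| f (assumed) | controls complete | controls leave at half the share | equal exits |
|---|---|---|---|
| 5% | 0.975 | 0.975/0.9875 = 0.99 | 1.00 |
| 10% | 0.95 | 0.95/0.975 = 0.97 | 1.00 |
| 19.3% | 0.90 | 0.903/0.952 = 0.95 | 1.00 |

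In events: uniform entry (an assumption) gives a mean of about 13.6 months. At the two hospital stays per year mentioned in the Background, controls have 2 × 13.6/12 = 2.27 stays. With f = 10%, intervention participants have 12.92 months and 2.15 stays. The ratio is 0.95.

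**Same case per person-time.** Numerator and denominator both shrink by 1 − f/2, so the rate ratio is 1.00 throughout. This holds only under the constant rate and risk-independent exit assumed above. If people leave because they are deteriorating, the rate is biased too.

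**The case against.** The strongest reply is that the article names what is counted and leaves the model open. A number of stays remains the outcome in a count model with a time offset, and an offset may stand in an analysis plan that is not shown. A reader might infer that the plan intends an unadjusted comparison of raw totals; the article does not say so. But the open choice of model does not settle the matter: the outcome definition itself has no time base, and the exit rules are written for one group only.

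A reader might also infer that observation is cut short only in the intervention group. That goes too far. Death is the first reason named for the attrition allowance, leaving the insurer is the only example of exclusion, and both also end a control's claims record. Only consent withdrawal and loss of the other criteria are plausibly one-sided, and the article gives no frequency for them.

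Nor does staggered entry bias the comparison by itself, if controls take over their match's entry date. The wording on the pre-observation period suggests such an anchor but does not state it for follow-up.

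Finally, exclusion from the study could mean that leavers are dropped from the analysis altogether. Truncated counts would then disappear, but a selected group of stayers would remain. The article does not say which is meant.

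**Conclusion.** The point holds as a defect in the definition of the primary outcomes, together with one-sided exit rules; it should be corrected. The 6.0-to-21.2-month spread is certain from the stated dates. The bias is conditional: it arises if exits are more frequent in the intervention group and numbers and totals are compared as defined. Its direction then favours the programme.

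Its size cannot be derived from the documents. Under the assumptions shown, the spurious reduction in mean counts is about 2.5% to 10% for one-sided exits of 5% to 19%, less if controls also leave, and nil if exits are equal. The 19% case assigns the plan's whole attrition allowance, deaths included, to one group and is therefore an upper bound. A reader might take the 25 percent extra recruitment as the exit share and arrive at 1 − 0.25/2 = 0.875. That figure is not supported, because 25 percent is added to 1,210 and corresponds to 19.3% of 1,500. These ratios should also not be set directly against the planned reduction from 20% to 15%, which the sample size treats as proportions and not as mean counts.

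**What to change.** - In Table 1 and the Health insurance perspective text, define stays, inpatient days, emergency responses and costs per insured person-time: count models with log insured days as offset, and costs per insured month.
- Start each matched set at the participant's programme entry date, and apply one end rule to both groups: death, leaving the insurer, or 31 December 2025.
- In Participants, separate leaving the programme from ending claims follow-up. Keep those who leave the programme or lose another criterion in the claims follow-up where consent allows.
- Where data must end because consent is withdrawn, end the matched control's observation on the same day. Report exits by reason and a sensitivity analysis, because neither an offset nor same-day ending corrects informative exit.

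The cost is a change of wording, a small loss of control observation time and a little more analysis. Insured days should be obtainable from the enrollee data already planned.

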#### Patient perspective

 On the patient level, health, well-being, and care dependency will be evaluated in a pre-post-design, using data from the intervention group as well as the control group 2 (*n* = 300). Seven questions compiled on the basis of clinical experience will be used to assess general health. The participants of the intervention and control group 2 will be asked weekly about falls, pain, urinary excretion, restlessness, shortness of breath, dizziness, and an open-ended question about any health problems experienced within the last seven days. The Quality of Life-Alzheimer’s Disease (QoL-AD) [23–26] is used to assess cognitive functioning in week 2-4 and 3-6 months after starting participation. Within 13 items, it covers physical health, energy, mood, living situation, memory, family, marriage, friends, chores, joy, money, own self, and life in general. QoL-AD possesses a good content, criterion concurrent and construct validity, as well as an excellent interrater reliability (Cohen's κ
> 0.70) and internal consistency (Cronbach's α
= 0.82) [24].Quality of life will be assessed using the Wellbeing measures in primary health care (WHO-5) questionnaire, containing five questions about mental well-being, like being in a good mood, feeling energetic, or being interested in daily life [27–29]. WHO-5 has satisfactory psychometric properties, both in terms of reliability (e.g. internal consistency α
=.92, split-half reliability *r*_*tt*_= .87), construct and factorial validity [29]. The Oslo social support scale (OSSS-3) will be used to assess social support through three questions about relationships with close individuals and the availability of neighborly help [30, 31]. Its predictive and construct validity is reported to be good, while internal consistency (α = .640) is acceptable [30]. Moreover, the UCLA Loneliness Scale is added to measure loneliness within 20 items, evaluating topics like social isolation, companionship, and perceived social support [32]. Existing validation studies come to favorable assessments with regard to criterion, convergent and discriminant construct validity, as well as reliability (retest reliability >.70, internal consistency α
=.89, split-half reliability *r*_*tt*_=.85) [32]. The WHO-5 questionnaire, OSSS-3 and the UCLA Loneliness Scale will be conducted in week 2-4 as well as 3-6 months after beginning to participate.

Care dependency will be assessed using the Barthel-Index [33, 34]. Here, ten activities of daily living are assessed regarding the capability of conducting them independently. Participants will conduct the assessment in week 2-4 and 3-6 months after enrolment into the study.

#### Health care provider perspective

On the health care provider level, aspects concerning interdisciplinary cooperation, suitability for the task, and usability will be assessed. According to the cooperation model, successful interdisciplinary cooperation requires support for three subprocesses: coordination, communication, and knowledge integration [35]. These topics will be evaluated using custom-designed questionnaires and interaction protocols derived from the diary.

To assess interdisciplinary cooperation, interaction protocols will be used to examine the content and timing of care during an STH event. For this purpose, all interactions of the respective stakeholders are recorded and stored by the digital interactive patient diary and analyzed using process mining methods [36]. The analysis will be initially carried out every 3 months. As the frequency of events increases, the evaluation will be switched to monthly.

Regarding the suitability/effectiveness of process and task integration, the adequacy of communication support among healthcare providers through the digital interactive health diary, and its facilitation of knowledge integration will be evaluated using a questionnaire. Additionally, we will assess the extent to which the digital interactive health diary assists users in task execution (suitability for the task) using our own designed questions. These evaluations will focus on the timely detection of health status deviations, the accuracy of their urgency and relevance assessment, and the successful assistance of patients during emergencies. Every three months, every stakeholder (the patients, caregivers, and healthcare providers) will receive two questions on communication/knowledge integration and two questions on task appropriateness in the diary, which are adapted to their subtasks in the STH program. In addition, following an STH event, the stakeholders are asked to evaluate the course of care during an STH event. In case of a low rating, possible causes (text modules for selection and free text field) are recorded. The results will help us to identify possible weaknesses at an early stage and to rectify them promptly with suitable measures.

The usability of the digital interactive health diary will be assessed quarterly using a tailored questionnaire by the German Social Accident Insurance Institution for the Health and Welfare services (BGW) [37]. It evaluates suitability, ease of use, long-term adoption potential, workflow and technical adaptation, preference for healthcare with the digital interactive health diary, and clarity of screen content.

###  Analysis

#### Health insurance perspective

Concerning the perspective of health insurance, the control group 1 will be matched through propensity score matching, incorporating sociodemographic variables such as age, gender, level of care dependency, region, as well as morbidity and healthcare utilization in the 12 to 24 months prior to the study commencement. Analyses will focus on differences in the utilization of inpatient and emergency services between the intervention and control groups. Moreover, the study will assess ambulatory-sensitive utilization of inpatient and emergency services. Total costs for the new form of healthcare in addition to costs for standard care will be calculated and compared to the cost savings of standard care. The statistical analyses will be descriptive and inferential, with regression models selected based on data requirements. Additionally, a cost-effectiveness analysis will be conducted.

#### Patient perspective

For the analyses on the patient level, the development of general health, care dependency and well-being will be evaluated over the period of the study (pre-post-comparison) both descriptively and inferentially. Regression models will be selected based on data requirements. Age, female gender, and lower educational attainment [38] are associated with increased morbidity [39], thus these variables will be included as covariates. The control group 2 follows the same inclusion criteria as the intervention group regarding age, level of care dependency and region.

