For the control group from the health insurance data (control group 1), insured individuals with similar characteristics to those in the intervention group will be identified from the enrollee and billing data of the participating health insurance companies. For better comparability, the aim is for the control group to also originate from Berlin, Germany. However, if the numbers are not sufficient, patients from structurally similar settlement areas will be included in the control group. A minimum 1:1 matching is planned, ensuring that the control group will be the same size as the intervention group. Depending on the number of insured individuals in the participating health insurance companies, a 1:n matching may also be performed, thereby increasing the size of the control group accordingly.

The control group for the secondary outcomes (control group 2) will be *n* = 300.

The rationale of this study is to select control groups that do not receive the intervention and an intervention group that does. It is based on the study's objective to assess the efficacy of the intervention in comparison to no treatment. For the control group 2 individuals with similar characteristics to those in the intervention group, but being insured by other than the participating health insurance companies, will be included in the study. This design allows it to determine the direct impact of the intervention by observing differences between the groups. The use of two no-intervention control groups is ethically justifiable in this context, as the expected benefits of the intervention are hypothesized but not yet established. This approach ensures that any observed effects can be attributed specifically to the intervention, thereby providing clear insights into its potential benefits.

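### Care level is neither balanced between the intervention group and control group 2 nor named as a covariate, so a different care-level mix can bias the estimated difference in patient-reported change

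*Protocol article*

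**What the plan says.** The Participants section sets the care-dependency criterion as a floor. Participants must "have been either officially granted “care level” 1 or higher", or "have applied for it or been assessed by their GP as needing" such a level. The same section explains that "five “care levels” represent a scale used to classify the level of care needed by individuals requiring long-term care". Eligible people therefore range from those with no formal level yet to those at level 5.

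On the composition of control group 2, Participants describes the people to be enrolled, who come from insurers outside the project, as follows: "For the control group 2 individuals with similar characteristics to those in the intervention group, but being insured by other than the participating health insurance". Analysis, Patient perspective, adds: "The control group 2 follows the same inclusion criteria as the intervention group regarding age, level of care dependency and region". Neither place states matching, weighting or any other balancing on care level.

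For the models, Analysis, Patient perspective, says: "Age, female gender, and lower educational attainment [38] are associated with increased morbidity [39], thus these variables will be included as covariates". The type of regression model is left to be chosen according to the data.

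For control group 1, Analysis, Health insurance perspective, plans propensity score matching "incorporating sociodemographic variables such as age, gender, level of care dependency, region, as well as morbidity and healthcare utilization" before the study.

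**The concern.** A shared entry threshold limits the range of care dependency in both groups but does not make the distribution within that range alike. Control group 2 comes from other insurers, while the intervention group is enrolled through general practitioners or a study physician, so the two mixes may differ in either direction.

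The protocol gives a reason for its three covariates, namely their association with morbidity. Care level fits that reason at least as directly. The protocol also treats care level as a confounder for the claims outcomes, but does not name it for the comparison in which care dependency is itself an outcome (Barthel-Index).

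These outcomes are secondary, but they answer the aims on health, quality of life and care needs set out under Objective. In a non-randomized comparison, a confounder named in advance protects better than one added once the data have been seen.

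**Working it through.** **The plan's own figures.** The article gives no sample size, expected effect or variance for the comparison with control group 2. Its one calculated figure, 1,210 for hospitalization of 20% versus 15% at 90% power, reproduces (1,212 with pooled variance, 1,208 with unpooled variance, two-sided 0.05). It does not bear on this point.

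**When a mix difference causes bias.** Suppose the share of people with high care levels differs between the groups by m, and mean change differs by d points between low (1–2) and high (3–5) care levels. With no true effect, the expected difference in mean change is m × d. If d = 0, the bias is zero however different the mix, because a constant level difference cancels in change scores.

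**Illustration on change scores.**

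- From the documents: planned group sizes of 1,500 and 300; significance level 0.05, taken as two-sided.
- Assumed: SD of change 10; m of 0.10, 0.20 or 0.30; d of 1 or 3 points.
- SE = 10 × √(1/1500 + 1/300) = 0.632.
- False-positive rate = P(|Z + m·d/SE| > 1.96), with Z standard normal.

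| d | m | Bias (points) | Bias/SE | False-positive rate |
|---|---|---|---|---|
| 1 | 0.10 | 0.1 | 0.158 | 5.3% |
| 1 | 0.20 | 0.2 | 0.316 | 6.2% |
| 1 | 0.30 | 0.3 | 0.474 | 7.6% |
| 3 | 0.10 | 0.3 | 0.474 | 7.6% |
| 3 | 0.20 | 0.6 | 0.949 | 15.8% |
| 3 | 0.30 | 0.9 | 1.423 | 29.6% |

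With attrition to 1,210 and 240 (the second figure is assumed), SE = 0.707 and the rates for d = 3 are 7.1%, 13.6% and 24.7%.

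**Simulation by type of model.** No true effect; 1,500 versus 300; 400 runs per setting. Assumed mixes over levels 1–5 were 10/40/30/15/5% (intervention) and 20/45/25/8/2% (control). The mean levels are 2.65 and 2.27, a difference of 0.38. Each level was assumed to lower the score by 0.5 units, with an outcome SD of about 0.9. Extra decline per level was 0, 0.05 or 0.10 units.

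| Model | Bias (units) | False-positive rate |
|---|---|---|
| Follow-up only | −0.19 to −0.23 | 90–98% |
| Change score | 0.00 to −0.04 | 5–13% |
| Adjusted for first score | −0.05 to −0.07 | 24–45% |
| Change score plus care level | 0.00 | 4–6% |
| Adjusted for first score plus care level | 0.00 | 4–6% |

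The follow-up-only row is a reference, not the plan, which describes a pre-post comparison. The third row is biased even when decline does not depend on care level, because the first score measures the underlying state with error. Adding care level removed the bias in every setting tried.

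**Scale.** With 1,500 and 300, the standardized difference detectable at 80% power is (1.96 + 0.84) × √(1/1500 + 1/300) = 0.18. In the first illustration the bias is 0.01 to 0.09 SD of change, so at the upper end it reaches about half of that.

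**The case against.** A reader might infer that the models will adjust for these three variables and nothing else, and that any difference in care-level mix will therefore be taken for an effect of the intervention. The article supports neither step. It says the three variables will be included, not that others are excluded, and it leaves the model open. The comparison is pre-post with a concurrent control, so a constant difference in level drops out of change scores. The groups also share age and region criteria and are meant to be similar, so having only a threshold in common is true of care dependency alone.

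Nor does the article say that people with higher care levels decline faster, or by how much between weeks 2–4 and months 3–6. Every size given here is assumed, and with a 1-point differential the false-positive rate stays close to nominal.

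It can also be argued that a full covariate list belongs in an analysis plan that is not shown. That is fair for detail such as the exact model form. It does not dispose of the point: the article states a covariate set and its reason, and that set omits a variable the same article uses to match control group 1. Leaving the model open is not a commitment to include care level.

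**Conclusion.** The point holds as a risk of bias, not as a demonstrated bias. Care level is not balanced between the intervention group and control group 2 beyond a shared floor, and it is not among the covariates named, whereas the claims comparison matches on it. Bias in the difference in change requires that the mixes differ and, in addition, that change depends on care level or that adjustment for the first score is imperfect.

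Its size cannot be derived from the documents. Under the assumptions shown, the false-positive rate is about 5–8% for a 1-point differential and about 8–30% for a 3-point differential. The affected outcomes are secondary but correspond to stated aims. The change is cheap and worth making.

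**What to change.** In Analysis, Patient perspective, add care level at entry (none or applied for, 1, 2, 3, 4, 5) to the named covariates of every model comparing the intervention group with control group 2. Alternatively, weight control group 2 to the care-level distribution of the intervention group. Either brings this comparison into line with the matching of control group 1.

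Adjustment for the first score of each scale is optional. That score is taken in weeks 2–4 of the intervention (Study period), so it must be interpreted as a measurement made after the start and cannot stand in for care level.

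The cost is one sentence in the analysis section and a few degrees of freedom. Data sources lists level of care among the diary entries but does not say that the exact level is recorded for control group 2. If it is not, one screening or survey item is needed. Recruitment quotas on care level are not recommended: enrolment is gradual over six quarters, so the mix they would have to mirror is not known while the controls are being recruited.
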